**GENERAL INFORMATION**

# 1. SUMMARY

**Introduction:** Postoperative nausea and vomiting (PONV) is among the most common postoperative complications, which gives patients extremely afflictive medical experience and sometimes intractable side-effect, leading to prolonged hospitalization, increased medical expenses and lower surgical satisfaction. PONV prophylaxis has been included in enhanced recovery after surgery (ERAS) management strategy. Even though the incidence of PONV can be decreased by using less of opioid and inhalational anesthetics and/or using antiemetic drugs, its occurrence is still high up to 20% in high-risk patients. Complementary to the antiemetic drugs, non-pharmacotherapy acupuncture treatment, represented by transcutaneous electrical acupoint stimulation (TEAS), has been used to prevent PONV occurrence. However, its effectiveness in preventing PONV has not been established yet due to small sampling size and not well controlled in the previous studies.

**Hypothesis:** TEAS treatment based on standardized antiemetic prophylaxis significantly lowers PONV incidence than the Sham treatment.

**Primary outcome:** PONV incidence

**Secondary outcomes:** PONV quantitative indicators including the time and VAS score of first nausea and vomiting, the times and VAS scores of each nausea and vomiting within 24 h after surgery; ERAS items including the 40-item Quality of Recovery (QoR-40) within 24 h, PONV related complications.

**Methods:** A multicenter, prospective, evaluator-blinded, parallel-group, randomized controlled trial (RCT) is administered in Sham or TEAS treatment on laparoscopic non-gastrointestinal surgery patients.

**Number of patients:** The number of patients to be included 1655 cases in total.

**Inclusion criteria:** 1) selective laparoscopic non-gastrointestinal surgery under general anesthesia; 2) age 18–50 years, BMI 15–40 kg/m2, ASA class I–III; 3) Apfel score ≥3 points; 4) ability to understand, sign informed consent and coordinate intervention and evaluation.

**Exclusion criteria:** 1) pregnancy and breast-feeding patients; 2) TEAS contraindications: skin allergy, breakage, infection or itching of test points, allergic to adhesive tape, pacemaker implanted; 3) history of alcohol, opioids or other drug abuse; 4) likely admission to ICU after surgery; 5) participation in other clinical studies within 3 months before admission to this study.

# 2. SCIENTIFIC RATIONALE AND GENERAL DESCRIPTION OF RESEARCH

PONV characterized as nausea, retching or vomiting or any these symptoms in combination after surgery, is one of the most common complaints after surgery with an overall incidence of 20%–30%(1, 2). Nausea gives patients extremely afflictive medical experience, induces the stomach discomfort including the feeling of keck and poor appetite, and even causes dizziness and headache. Vomiting increases the potential risks of electrolyte imbalances, pain, incision dehiscence or hernia, dehydration, esophageal damage or airway aspiration(3). The incidence in high-risk patients (more than 3 scores), classified by Apfel simplified score which is based on four independent risk predictors (female gender, nonsmoker, history of motion sickness or PONV, postoperative opioid use), is 61%–79%(4). With The combination of 2–3 kinds of antiemetic drugs for PONV, the incidence of high-risk patients had a significant decline, however, still as high as 20%(5). What's worse is that the actual incidence of PONV is even higher due to the loss to follow-up bias by traditional paper diaries(6). The multiple channel and sites of PONV could not be blocked by the single locus of antiemetic drugs(7). It is difficult to further reduce the incidence of PONV by adding different kinds or dosages of drugs for the remaining uncovered PONV sites and the saturation of receptors(8), while drug-related side effects are increasing gradually(9)，such as headaches, xerostomia, abnormal liver function, extrapyramidal reactions and other related side effects(9-11).

Complementary to the antiemetic drugs, non-pharmaceutical therapy including acupuncture provides considerable advantages in wide action range and non-toxic effects, which has been widely used in postoperative pain analgesia and gastrointestinal function rehabilitation(12, 13). Acupuncture, a safe and effective non-pharmacotherapy, can directly or indirectly inhibits the emesis center or regulates gastrointestinal function through multiple regulatory mechanism, such as modulating gastric motility through somatovisceral reflex, influencing the endogenous opioid system and serotonin transmission(14-17). Transcutaneous electrical acupoint stimulation (TEAS) with transcutaneous electrical nerve stimulation applied to acupuncture points has been used to prevent PONV occurrence(18, 19). However, its effectiveness in preventing PONV has not been established yet due to small sampling size and not well controlled in the previous studies(20). Therefore, the large sample size, multicenter, evaluator-blinded, and randomized controlled study were carried out to verify the effectiveness of TEAS in reducing the incidence of PONV.

# 3. RESEARCH OBJECTIVES

This trial aims to assess the preventive effectiveness of transcutaneous electrical acupoint stimulation (TEAS) on the incidence of PONV in high-risk surgical patients.

# 4. RESEARCH DESIGN

# 4.1 Type of study

This work is a multicenter, prospective, evaluator-blinded, parallel-group, RCT. Using Crabyter scientific research system (Xinyu Information Technology Co., Ltd), the enrolled patients will be randomly divided into Sham and TEAS groups in a 1:1 ratio, with four patients regarded as a block, and obtain the random number.

# 4.2 Primary and Secondary outcomes

# 4.2.1 Baseline information

Demographic information (age, sex, height, weight, education, occupation, etc.), preoperative information (biochemical indicators, comorbidities, anxiety scores, etc.), surgical and anesthetic information (operation name and period, amount of access, RASS score, dosage of analgesics and antiemetics, etc.) will be compared in the two groups.

# 4.2.2 Primary outcome

In this study, at least once nausea, retching or vomiting after operation, or any combination of the above symptoms within 24 h after surgery is taken as the diagnostic criteria of PONV, thereby setting PONV incidence 24h as a primary outcome.

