### Prescreening and rescreening

All investigators will be trained and will follow the trial protocol. Researchers will assess whether the scheduled patient meets the criteria one day before the surgery. Informed consent will be signed if the patient meets the eligibility, and then make an evaluation of self-rating anxiety scale (SAS). Patients’ eligibility for recruitment will be reassessed after extubation. The patients given conversion to open laparotomy, occurring skin allergy, breakage, infection or itching of test points, refusing to participate or unplanned admission to ICU will be excluded from the trial. If they are eligible, randomization will be performed. Using Crabyter scientific research system (Xinyu Information Technology Co., Ltd) for block randomization, the enrolled patients will be randomly divided into Sham and TEAS groups in a 1:1 ratio (with a block size of 4) to verify the reliability of TEAS in PONV prevention. The enrolled patients will be assessed by Richmond Agitation-Sedation Scale (RASS).

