### 4.3.3 Pharmacologic and non-pharmacologic intervention

Attending anesthesiologists administrated PONV prophylaxis in operation room. Dexamethasone 5 mg IV and the second-generation 5-hydroxytryptamine 3 (5-HT3) receptor antagonists palonosetron 0.075 mg are administrated before anesthesia induction as the first choice. When palonosetron was not available at some hospitals, patients received dexamethasone 5 mg (before induction) combined with tropisetron 2 mg (at the end of surgery) instead. According to the criteria of WHO acupuncture points, Neiguan (P6) and Zusanli (ST36) will be selected in this study. As shown in the Supplementary Figure 1, these acupoints are far from the operation site. P6 is located at 2 inches above palm wrist transverse striation, between the palm long tendon and the temporal flexor tendon. ST36 is located at 3 inches below EX-LE5 (the lateral pit of the patella and patellar ligament), and one transverse finger outward lateral tibia. The electrode slice has a single conductive emboss and two connecting wires, thereby enabling non-invasive, accurate and convenient stimulation. The TEAS treatments will be scheduled to conduct twice in total, respectively during anesthesia recovery in PACU (to be awake and calm, RASS = 0) and in the next-morning of surgical ward for 30 minutes.

**TEAS group:** When patients recover from anesthesia status to a degree of the Steward recovery score ≥ 4 in PACU and the endotracheal tubes are withdrawn, the first TEAS treatment will be performed. The bilateral P6 and ST36 will be pressed to achieve a tingling sensation called “de qi”, and electrode slices will be stuck and fixed on those acupoints. Interveners will connect electrode slices to electrical stimulator and select the distant-dense wave with the frequency of 2/10Hz. After adjusting the intensity to the patient’s maximum tolerance, he/she will be treated for 30 minutes. Another TEAS treatment will be performed between 9 am and 12 am in the ward on the first postoperative day; meanwhile, patients will receive routine health education including illness, diet, exercise and psychological considerations.

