### 4.4.2 Blinding method

Patients will be blinded when being allocated and cannot detect any difference in the entire procedures. This procedure will be the same in both groups, except that the connecting wires inside the stimulators will be broken in the Sham group. Therapeutic evaluators will be blinded in the process of allocation, screening, intervention treatment and statistical analysis. To prevent the leakage of allocation, evaluator will not play any other roles in the study, and we will apply spatial and temporal isolation for interventions and evaluations. Interventions will be conducted in PACU and ward, whereas evaluations will be performed only in the ward. Interventions and evaluations will be performed during different periods in ward. Interventions will be conducted once a day between 9 am and 12 am in the ward, whereas evaluations will be performed after 12 am. When the patient is randomized, an evaluator will complete the entire process of evaluation in a blinded intervention progress. A random administrator will be selected from principle investigator research center. This administrator will not play any other roles in the study. The external statistical experts will be blinded to allocation, and the statistical calculations will be independently conducted.

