### 4.4.3 Follow-up

Electronic patient self-reported scale (Jiangsu Rehn Medtech Technology Co., Ltd) will be applied to evaluate and record the occurrence of PONV in real time, including the time to each PONV and corresponding VAS score. The VAS is a simple-to-use measure to evaluate intensity of PONV. It’s a 10-point numerical rating scale with 0 = “no nausea or vomiting” and 10 = “worst nausea imaginable and vomiting”. The cut points on the PONV VAS have been recommended: mild PONV ( 4), which has little impact on daily activities and does not affect sleep; severe PONV ( 7), which results in inability to sleep and seriously hinders daily life; moderate PONV, whose clinical influence intervenes between the two above. When PONV happens at any time, patients or their caregivers spontaneously assess the severity of PONV with VAS and then send it to the central server through the electronic scale. The evaluator port harvests PONV information immediately so that it can be managed timely. To ensure a blinded fashion, both groups will be evaluated by direct questioning in the ward after 12 am at the 1st and 2nd postoperative day in ward. Persistent nausea was defined as continuous nausea lasting over 5 min. If the patients are discharged on the second day postoperative, they will be assessed by telephone. The postoperative 30-day information about delayed curative efficacy, complications and adverse events will be obtained through telephone follow-ups and electronic medical record system.

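### The 24 h primary outcome counts PONV from the end of surgery, but randomisation comes later in PACU, so episodes that allocation cannot affect count as cases in both arms

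*Protocol*

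**What the plan says.** Protocol section 4.2.2 makes a patient a primary-outcome case if there is "at least once nausea, retching or vomiting after operation, or any combination of the above symptoms within 24 h after surgery". The clock is tied to surgery, and one episode settles the binary outcome.

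Allocation comes later. Under the heading Prescreening and rescreening, "eligibility for recruitment will be reassessed after extubation", and then "If they are eligible, randomization will be performed". Table 1 in section 4.5 puts rescreening and randomisation in the PACU column. The exclusions applied at rescreening are "conversion to open laparotomy, occurring skin allergy, breakage, infection or itching of test points, refusing to participate or unplanned admission to ICU"; PONV already present is not among them. Section 4.2.1 does not name it among the baseline items.

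The first session follows in PACU. Section 4.3.3 gives the timing as "respectively during anesthesia recovery in PACU (to be awake and calm, RASS = 0") and adds, for the TEAS arm, a Steward score of at least 4 and that once "the endotracheal tubes are withdrawn, the first TEAS treatment will be performed".

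On capture, section 4.4.2 says "evaluations will be performed only in the ward". Section 4.4.3 also provides an electronic self-report scale with a time for each episode: "When PONV happens at any time, patients or their caregivers spontaneously assess the severity of PONV". Section 9 keeps all subjects under the ITT principle. Nothing in the protocol limits the outcome to onset after randomisation.

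**The concern.** The stated objective in section 3 is the preventive effectiveness of TEAS. Between the end of surgery and randomisation there is an interval in which outcome events count although no arm has been assigned. A patient who is nauseated or vomits in that interval is already a case, and nothing done afterwards can change that.

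Such episodes should occur equally often in the two arms. They add the same amount to both incidences and leave less room for a difference. At stake is dilution of the effect and some loss of power, in a design whose evaluable number per arm is set at 80% power for the planned effect. The protocol itself fixes the outcome window, so this is not a detail that an SAP would be expected to supply.

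**Working it through.** **Sequence.** End of surgery (outcome clock starts), extubation, rescreening, randomisation, first session. The protocol does not give the length of the interval before randomisation or how often PONV occurs in it. It does not define the zero time more closely than after operation or after surgery.

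**Inputs from section 9.** Control incidence 40%; reduction 7 points, so 33% and a relative risk of 0.33/0.40 = 0.825; significance level 0.05; power 80%; 742 per arm.

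**Reproducing the plan's figure.** Two-sided test of two proportions, pooled variance under the null, no continuity correction, with p̄ = (p1 + p2)/2:

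n = [1.960·√(2p̄(1−p̄)) + 0.842·√(p1(1−p1) + p2(1−p2))]² / (p1 − p2)²

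With p1 = 0.40, p2 = 0.33 and p̄ = 0.365, the roots are 0.6808 and 0.6790, so n = 741.3, rounded up to 742. This matches the plan, and power at 742 is 80.0%.

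**Dilution.** Let f be the share of Sham cases whose first episode comes before treatment could act. The protocol gives no value, so f is an assumption. Assume also that the total Sham incidence stays at 40% and that 0.825 acts only on later first episodes:

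- early incidence in both arms = 0.40·f
- TEAS incidence = 0.40·f + (0.40 − 0.40·f)·0.825
- power = Φ{[(p1 − p2)·√n − 1.960·√(2p̄(1−p̄))] / √(p1(1−p1) + p2(1−p2))}

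| f | Early, both arms | TEAS total | Difference | Power, 742 per arm | Power, 817 per arm |
|---|---|---|---|---|---|
| 0 | 0% | 33.0% | 7.0 points | 80.0% | 83.7% |
| 5% | 2% | 33.35% | 6.65 points | 75.8% | 79.7% |
| 10% | 4% | 33.7% | 6.3 points | 71.1% | 75.2% |
| 20% | 8% | 34.4% | 5.6 points | 60.7% | 64.9% |

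The last column is half of the planned 1634, that is, no loss to follow-up. The 20% row shows how the result moves with f; nothing in the protocol suggests that value.

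**What a later start of the window recovers.** Take the least favourable case: every early case falls before randomisation and none has a later episode. The early events drop out of both arms. The difference stays the same, but the incidences and their variance fall.

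| f | Sham | TEAS | Difference | Power, 742 per arm | Gain |
|---|---|---|---|---|---|
| 5% | 38.0% | 31.35% | 6.65 points | 76.8% | 1.0 point |
| 10% | 36.0% | 29.7% | 6.3 points | 73.4% | 2.3 points |
| 20% | 32.0% | 26.4% | 5.6 points | 66.0% | 5.3 points |

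The gain is larger if early cases also have later episodes that TEAS can prevent. In this model power returns to 80% only if every early Sham case has a later episode.

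**Scope of f.** The calculation counts everything before treatment could act. Episodes between randomisation and the first session would be part of that, but they belong in an ITT comparison and the later start does not remove them.

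**The case against.** Four points on the other side carry weight.

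1. The 40% and the 7-point reduction come from a cited meta-analysis of TEAS trials. If those trials counted from the end of surgery with a similar start of treatment, the dilution is already inside the 7 points, and deducting it again would count it twice. The protocol does not say. This stands, and it makes the power figures conditional.

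2. The early share may be close to zero. For part of the interval the patient is anaesthetised and intubated, and randomisation follows in PACU. This stands as to size. It does not alter the fact that the definition counts such episodes.

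3. Because evaluations take place only in the ward, a reader might infer that PACU episodes are known only by later recall and cannot be timed. The protocol does not support that. The ward restriction concerns the blinded evaluators, while the electronic scale in section 4.4.3 records the time of each episode. The protocol does not say whether the scale runs in PACU, so capture of early episodes is unclear, not impossible.

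4. Counting from the end of surgery fits the protocol's own description of PONV in section 2 and eases comparison with other studies. This stands as a reason to keep that window as a supporting analysis.

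A reader might also infer that the early episodes bias the comparison toward one arm. They precede allocation, so they are expected equally in both.

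**Conclusion.** The mismatch is real and follows from the protocol's text: the primary outcome includes episodes that occur before the patient has an arm. The direction is toward no difference, and neither arm is favoured.

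The size cannot be derived from the document. With an assumed 5% to 10% of Sham cases having their first episode before treatment could act, and 0.825 applying only to later first episodes, power at 742 per arm is 76% to 71% instead of 80%. It is nearer 80%, or unchanged, if the planning figures already contain such events or if the early share is very small.

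Two stronger conclusions are tempting and are not supported: that the trial is shown to be underpowered, and that moving the start of the window restores 80%. The first depends on an unknown share and on how the cited studies counted; the second needs early cases to have later episodes. The point deserves correction because the change is cheap and makes the outcome match the question. It does not invalidate the randomised comparison.

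**What to change.** - Define the primary outcome as nausea, retching or vomiting with onset from randomisation to 24 h after surgery.
- Add PONV status (yes/no, with time) to the existing PACU rescreening form, completed before allocation, and use it as a baseline covariate.
- State how nausea that continues through randomisation is classified.
- Keep the end-of-surgery window as a sensitivity analysis.
- State whether the electronic scale is in use in PACU.

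The cost is some outcome wording and one form item. The downside is a slightly lower incidence and less comparability with studies that count from the end of surgery, which the sensitivity analysis largely covers. In return, the primary outcome contains only events that allocation can change, and the unknown early share is observed. If early cases have no later episode, the recovery of power is about 1 to 2 percentage points at an early share of 5% to 10%; it is more if they do.

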# 4.2.3 Secondary outcome

Secondary research indicators are PONV quantitative indicators and ERAS-related items. PONV quantitative indicators include the time and visual analogue scale (VAS) score of first PONV, the cumulative times and the highest VAS score of nausea and vomiting within 24 h after surgery. ERAS items include the 40-item Quality of Recovery (QoR-40) within 24 h, PONV related complications and postoperative hospital stay. The specific contents of QoR-40 score include five aspects: physical comfort (12 items, 60 scores), emotional state (9 items, 45 scores), physical independence (5 items, 25 scores), psychological support (7 items, 35 scores) and pain (7 items, 35 scores)(21). PONV related complications are dizziness and headache, electrolyte imbalances and pain.

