### 9. STATISTICAL ANALYSIS

**Sample size estimation and data analysis：**In previous studies, the PONV incidence was reported to be approximately 40%, and the PONV incidence was reduced by 7% with the TEAS treatment(19). With a significance set at 0.05, power set at 80%, the sample size required to detect differences was 742 patients in each group calculated with the Pass 11 software (NCSS, LLC. Kaysville, Utah, USA). Taking into account a loss-to-follow-up rate of about 10%, 1634 patients in total were enrolled to meet the minimum sample size requirement.

**Sample distribution:** Describes the size and loss rate of each data set, and provides detailed reasons for loss.

**Data comparability:** Preoperative baseline information, surgical information, anesthetic and antiemetic drug usage are compared between the two groups.

**Validity analysis:** The primary and secondary outcomes of the two groups are compared.

**Safety analysis:** Chi-square statistical tests are performed for the number and incidence of adverse events.

According to the intentionality analysis ITT principle, all subjects are included even if they have undergone in part of the trial process. At the same time, the efficacy and safety indicators will be included into the PP data set conformed to the schemed set, and then statistically analyzed in strict accordance with the scheme. Continuous variables will be described by means (SDs) and median (IQR), the differences between the two groups will be compared using the independent-sample T test. Categorical variables will be described by numbers (percentages), and chi-square test and Fisher's accuracy test will be used to test the incidence. Nonparametric rank sum test will be used for the grade data. *P value*<.05 will be considered statistically significant. All statistical analyses will be performed using SPSS software (version 25.0, IBM Corporation).

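### QoR-40 would be compared by an unadjusted t test although a preoperative anxiety score is already collected; ANCOVA on that score could gain some precision at almost no cost.

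*Protocol*

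**What the plan says.** - **Outcome.** Protocol section 4.2.3 places QoR-40 among three ERAS items: "ERAS items include the 40-item Quality of Recovery (QoR-40) within 24 h", followed by complications of PONV and length of hospital stay. The items are not ranked. The section also gives the domain structure, beginning "physical comfort (12 items, 60 scores), emotional state (9 items, 45 scores), physical independence (5 items, 25 scores", then psychological support (7 items, 35 points) and pain (7 items, 35 points).
- **Test.** Section 9 sets general rules by type of variable. For continuous variables, "the differences between the two groups will be compared using the independent-sample T test". For ordered categories, "Nonparametric rank sum test will be used for the grade data". Neither rule names a covariate, and neither mentions QoR-40.
- **Anxiety score.** Under Prescreening and rescreening, once consent is signed on the day before surgery, researchers "make an evaluation of self-rating anxiety scale (SAS"). Table 1 shows SAS one day before the operation and randomisation later, in the PACU.
- **Use of the anxiety score.** Section 4.2.1 lists it with the items to be compared between groups: "preoperative information (biochemical indicators, comorbidities, anxiety scores, etc".). The data comparability paragraph of section 9 likewise compares preoperative information between the arms. No other use is stated.

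**The concern.** SAS is measured before allocation, so treatment cannot affect it, and it can properly be used as a covariate. It is also plausibly related to the outcome: emotional state and psychological support carry 45 + 35 = 80 of the 200 QoR-40 points. The protocol collects the score and then uses it only to describe and compare the arms.

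A baseline comparison does nothing for the precision of the treatment effect, whereas including the same score in the outcome model can. What is at stake is the width of the confidence interval for one secondary outcome. The validity of the comparison and the primary outcome are not affected.

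**Working it through.** **Inputs from the protocol**
- Sample size (section 9): 40% PONV, reduced by 7 percentage points, significance level 0.05, power 80%, 742 per arm.
- QoR-40 scale (section 4.2.3): 12 + 9 + 5 + 7 + 7 = 40 items and 60 + 45 + 25 + 35 + 35 = 200 points. A total on this range is naturally read as a continuous variable.

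**Inputs assumed**
- Correlation r between preoperative SAS and 24 h QoR-40: 0.2, 0.3 or 0.4. The protocol gives no value.
- QoR-40 available in 742 patients per arm, the number planned for PONV. The protocol gives no SD, effect or power for QoR-40, so results are in SD units.

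**Step 1: the protocol's own figure.** Two proportions, 0.40 and 0.33, two-sided 0.05, pooled variance under the null, mean proportion 0.365:

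n = [1.960 × √(2 × 0.365 × 0.635) + 0.842 × √(0.40 × 0.60 + 0.33 × 0.67)]² / 0.07² = 742 after rounding up.

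The stated 742 is reproduced. It concerns PONV only.

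**Step 2: the unadjusted t test for QoR-40.** The variance of the difference is 2 × SD² / n.
- Detectable difference at 80% power: (1.960 + 0.842) × √(2/742) = 0.145 SD.
- Half-width of the 95% confidence interval: 1.960 × √(2/742) = 0.102 SD.

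**Step 3: ANCOVA with SAS.** The variance is multiplied by 1 − r², and the standard error and detectable difference by √(1 − r²). The equivalent unadjusted sample size is 742 / (1 − r²).

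| Assumed r | Variance factor | Fall in variance | Fall in standard error | Detectable difference | Equivalent n per arm | Power at 0.145 SD |
|---|---|---|---|---|---|---|
| none (t test) | 1.00 | – | – | 0.145 SD | 742 | 80% |
| 0.2 | 0.96 | 4% | 2% | 0.143 SD | 773 | 82% |
| 0.3 | 0.91 | 9% | 5% | 0.139 SD | 815 | 84% |
| 0.4 | 0.84 | 16% | 8% | 0.133 SD | 883 | 86% |

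**Step 4: what adjustment costs if SAS is uninformative.** One residual degree of freedom, 1481 instead of 1482 at 742 per arm, which is negligible.

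**The case against.** The case against raising this is that nothing here is wrong. The t test is valid, QoR-40 is an unpowered secondary outcome, and covariate adjustment is often left to the statistical analysis plan, which is not at hand. The gain rests on a correlation that the protocol does not give, and with SAS alone it is probably small.

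Most of this stands and sets the priority. It does not remove the point, because section 9 states a test for continuous variables, and a near-free alternative using data already collected is better. If the analysis plan already adjusts QoR-40 for SAS, the point is settled.

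Three limits also follow from the text:
- **The t test is inferred.** It comes from the general rule for continuous variables. If QoR-40 were treated as graded data, the rank sum test would apply. That test is also unadjusted, but the variance formula above would not carry over directly.
- **Rank of the outcome.** A reader might infer that QoR-40 is the trial's main recovery outcome. Section 4.2.3 lists it as one of three ERAS items without ranking, and the objective and sample size concern PONV incidence.
- **Chance imbalance.** A reader might infer that, without adjustment, a chance difference in baseline mood or comfort could not be told apart from a TEAS effect. The standard error of a randomised comparison already allows for such imbalance. The issue is precision, not bias.

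A reader might also infer that the protocol should add a preoperative QoR-40, since Table 1 schedules none. The documents do not support making that part of this point. It would be a new assessment, and because eligibility is rechecked after extubation, it would also be completed by patients who are never randomised. Section 9 already describes enrolment in the past tense, so patients already enrolled might lack the value.

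**Conclusion.** The point holds as a modest efficiency suggestion. As the general rule reads, QoR-40 would be compared without adjustment, while a pre-randomisation score that may predict it is used only to compare the arms at baseline.

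If SAS correlates 0.2 to 0.4 with QoR-40, the variance falls by 4 to 16% and the standard error by about 2 to 8%. The detectable difference at 742 per arm then moves from 0.145 SD to between 0.143 and 0.133 SD. The range rests wholly on the assumed correlation, on QoR-40 being analysed as a continuous total, and on 742 analysed patients per arm. The true gain is unknown and may lie at or below the low end. The unadjusted result would remain valid, so the priority is low.

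**What to change.** In section 9, state that the QoR-40 total is analysed by ANCOVA with treatment group and preoperative SAS score as covariate, in place of the unadjusted t test. Report the adjusted mean difference with its 95% confidence interval, and fix this before unblinding. The same sentence settles which of the two general rules covers QoR-40.

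The cost is one sentence. SAS is already collected at an existing visit, and SPSS, the software named in section 9, fits the model. The sentence should also say how the occasional missing SAS value is handled, so that no randomised patient with a QoR-40 score drops out of the analysis.
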